## 2. LAY SUMMARY

Iron deficiency is the most common nutritional deficiency in the world. It is now recognized that iron deficiency can affect our health in many ways, impairing brain development and physical function, and worsening co-existing conditions such as heart and kidney disease. It is normally treated with oral iron tablets, which delivers iron gradually in ~65mg doses over a number of weeks. The amount of iron absorbed from these doses is carefully balanced with preventing excess iron uptake into the body. Too much iron can be harmful. In recent years, an alternative treatment based on intravenous iron (i.e. through a 'drip') has become increasingly common. This can be helpful in patients who are unable to take oral iron, or when there is a need for rapid treatment of iron deficiency e.g. before major surgery. In contrast to oral iron, intravenous iron safely delivers a large amount of iron (up to 2g) at once. It works quickly as it is delivered directly into the blood and bypasses the gut. While it is an efficient way of quickly correcting iron deficiency (i.e. restoring blood iron markers to normal values), we do not know where in the body this large quantity of iron ends up. This is an important question, because the human body is not capable of excreting iron. As a result, some of this extra iron may be deposited in vital organs like the liver, heart and spleen. We know from studying patients and animals with genetic iron overload disorders (e.g. hemochromatosis) that too much iron in these organs can be detrimental to health.

The aim of this study is to track where the iron goes in different tissues in the hours, days and weeks after an intravenous iron infusion. We can track iron in tissues by using sophisticated magnetic resonance imaging (MRI). This MRI technique is the gold standard technique for estimating tissue iron levels in patients. It collects certain relaxometry parameters R1/R2/R2\* (R2 star refers to a parameter derived from raw MRI data), which are well established as accurate indicators of tissue iron content. This is safe and doesn't involve any additional invasive procedures. We will include patients who have been prescribed intravenous iron as part of standard clinical care to treat their iron deficiency.

The information gained from this study will be used to design a larger study to investigate the potential toxic effects of intravenous iron infusion in different patient populations. Ultimately, the understanding gained from these studies will help us refine current treatments of iron deficiency to maximise the benefits and minimise the harms.

### 3. SYNOPSIS

|                                 |                                                                                                                                                         |                                                                                                                            |                                                                               |
|---------------------------------|---------------------------------------------------------------------------------------------------------------------------------------------------------|----------------------------------------------------------------------------------------------------------------------------|-------------------------------------------------------------------------------|
| Study Title                     | Study of Tissue Iron Uptake in Iron-Deficient Patients Receiving Intravenous Iron Replacement Therapy: A prospective observational Study (STUDY) |                                                                                                                            |                                                                               |
| Internal ref. no. / short title | Imaging intravenous iron                                                                                                                                |                                                                                                                            |                                                                               |
| Study registration              | We will register this study on ISRCTN following ethical approval and prior to recruitment of first participant.                                         |                                                                                                                            |                                                                               |
| Sponsor                         | University of Oxford, RGEA
[name],
[name],
[name],
[name]                                               |                                                                                                                            |                                                                               |
| Funder                          | BHF Centre of Research Excellence
Division of Cardiovascular Medicine
Direct line: [name]
[contact]                |                                                                                                                            |                                                                               |
| Study Design                    | Prospective, observational, cohort study                                                                                                                |                                                                                                                            |                                                                               |
| Study Participants              | Age >18 years, scheduled to receive intravenous iron therapy for correction of iron deficiency                                                          |                                                                                                                            |                                                                               |
| Sample Size                     | 12                                                                                                                                                      |                                                                                                                            |                                                                               |
| Planned Study Period            | 01-August-2022 to 31-July-2024                                                                                                                          |                                                                                                                            |                                                                               |
|                                 | Objectives                                                                                                                                              | Outcome Measures                                                                                                           | Timepoint(s)                                                                  |
| Primary                         | To establish the kinetics of iron uptake into the heart, liver, spleen, kidney, skeletal muscle and blood                                               | Changes from baseline in cardiac structure and function (Cine MRI) and multi-organ magnetic resonance relaxometries (delta | Baseline, prior to infusion (day 1)
Timepoint 1- 3hr post infusion (day 1) |

|                 |                                                                                                                                                  |                                                                                                                                                                                                                                                                           |                                                                                                                                                             |
|-----------------|--------------------------------------------------------------------------------------------------------------------------------------------------|---------------------------------------------------------------------------------------------------------------------------------------------------------------------------------------------------------------------------------------------------------------------------|-------------------------------------------------------------------------------------------------------------------------------------------------------------|
|                 | following a single intravenous iron infusion (Ferric carboxymaltose, Ferinject, 1000mg)                                                          | R1/R2/R2*) for each participant                                                                                                                                                                                                                                           | Timepoint 2- ~2 weeks post infusion
Timepoint 3- ~6 weeks post infusion                                                                                  |
| Secondary       | Determine the effects of iron infusion (Ferric carboxymaltose, Ferinject, 1000mg) on serum iron indices and serum markers of tissue iron damage. | Change from baseline in:
1. Serum iron indices: iron, ferritin, transferrin saturation, non-transferrin bound iron
2. Serum markers of tissue iron damage, including but not limited to lipid peroxidation markers malondialdehyde (MDA) and 4-Hydroxynonenal (HNE) | Baseline, prior to infusion (day 1)
Timepoint 1- 3hr post infusion (day 1)
Timepoint 2- ~2 weeks post infusion
Timepoint 3- ~6 weeks post infusion |
| Intervention(s) | None- This is a non-interventional observational study                                                                                           |                                                                                                                                                                                                                                                                           |                                                                                                                                                             |
| Comparator      | None                                                                                                                                             |                                                                                                                                                                                                                                                                           |                                                                                                                                                             |

\* - refers to a parameter derived from raw MRI data

#### 4. ABBREVIATIONS

|      |                                                               |
|------|---------------------------------------------------------------|
| CI   | Chief Investigator                                            |
| CRF  | Case Report Form                                              |
| GCP  | Good Clinical Practice                                        |
| GP   | General Practitioner                                          |
| HRA  | Health Research Authority                                     |
| ICF  | Informed Consent Form                                         |
| NHS  | National Health Service                                       |
| RES  | Research Ethics Service                                       |
| PI   | Principal Investigator                                        |
| PIL  | Participant/ Patient Information Leaflet                      |
| R&D  | NHS Trust R&D Department                                      |
| REC  | Research Ethics Committee                                     |
| RGEA | Research Governance, Ethics & Assurance, University of Oxford |
| SOP  | Standard Operating Procedure                                  |

|       |                                                  |
|-------|--------------------------------------------------|
| AHF   | Acute heart failure                              |
| CHF   | Chronic heart failure                            |
| I.V   | intravenous                                      |
| MRI   | Magnetic Resonance Imaging                       |
| OCMR  | Oxford Centre for Magnetic Resonance             |
| IDMS  | Iron Deficiency Management Service               |
| FCM   | Ferric carboxymaltose                            |
| NTBI  | Non-transferrin bound iron                       |
| OUHFT | Oxford University Hospitals NHS Foundation Trust |

## 5. BACKGROUND AND RATIONALE

**Iron deficiency**-The prevalence of non-anaemic iron deficiency is 1-2 billion worldwide. It has recently become recognised as an important co-morbidity in common conditions including acute and chronic heart failure (AHF and CHF). Traditionally, iron deficiency has been treated through oral iron supplementation.

**New treatment for iron deficiency**- The strategy for treating iron deficiency has been changed by our growing understanding of iron homeostasis. It is now recognised that the iron-homeostatic hormone hepcidin (which is raised in inflammatory conditions such as ACF and CHF) contributes to iron deficiency by blocking the sole mammalian iron exporter ferroportin in the gut and spleen, respective sites of iron absorption and recycling. These discoveries have driven the development, and now widespread use, of intravenous (I.V) iron (in-lieu of oral iron) to bypass blocked ferroportin in the gut. Some short-term trials have shown modest or no benefits of I.V iron on exercise capacity, risk of hospitalisation and of cardiovascular death in CHF and AHF. Despite this, the European Society of Cardiology (ESC) now recommends the use of I.V iron in all HF patients with iron deficiency. I.V iron is also increasingly being used for correction of iron deficiency in otherwise healthy individuals, as well as in critical care setting. Consequently, NHS expenditure on I.V iron has grown exponentially in recent years. However, there is a scarcity of data on the long-term effects and the mechanisms of action of I.V iron, and persisting safety concerns over increased risk of infection and organ iron toxicity.

**Key question with safety implications**- We do not know how I.V iron formulations affect myocardial iron levels and cardiac function in the long term. Answering these questions is important for ensuring that correction of iron deficiency is not accompanied by myocardial iron toxicity. It is widely assumed that I.V iron formulations such as Ferinject (ferric carboxymaltose or FCM) are taken up and degraded by macrophages, allowing slow and controlled release of iron into the circulation, and subsequent loading onto the plasma iron chaperone transferrin for uptake by tissues. Most tissues can prevent excess iron accumulation by downregulating the levels of transferrin receptor expression (this is achieved through the iron-sensing function of iron-regulatory proteins IRPs). However, kinetic studies of plasma iron indices, together with the speed of manifestation of associated physiological effects demonstrate that FCM infusion results in rapid and physiologically-relevant rise in non-transferrin bound iron (NTBI) in the plasma. Excess NTBI in the plasma is dangerous because it is taken up by tissues through L-type and T-type calcium channels, which are not regulated by IRPs. These channels are highly expressed in the heart and it is well established that they are responsible for the iron overload cardiomyopathy that occurs in genetic disorders of iron overload such as hemochromatosis (where NTBI is also raised). In pre-clinical mouse models, we found that a patient-equivalent dose of intravenous iron resulted in ~400% increase in cardiac iron levels.

**Study rationale** - This is a pump-priming study to establish if the standard intravenous iron treatment, given as part of standard clinical care to correct iron deficiency, results in an acute rise in tissue iron levels, including myocardial iron at the early timepoints, which would be evidence for the direct, rapid unregulated route of iron uptake. It is an observational cohort study measuring changes in tissue iron levels from baseline following infusion of intravenous iron. Tissue iron levels will naturally vary between individuals. Because of this, the study will not use a placebo arm. Instead, it will measure changes against baseline tissue iron levels.

**Value** - This work is a first and essential step towards understanding the effects of this emerging iron replacement therapy on tissue iron levels, and identifying the features that distinguish patients who will benefit from those who could be harmed by I.V iron treatment.

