## 9.8. Day 1 - Three-hour post IV iron infusion assessment

MRI scan (up to 1 hour)

- Cine imaging for cardiac structure and function
- Tissue characterisation by R1/R2/R2\* relaxometry of the heart, liver, spleen, blood and skeletal muscle

Blood samples:

- One sample collected for study investigations to measure serum iron indices and serum markers of tissue iron damage.

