### 11.1. Description of the Statistical Methods

The primary outcome is the absolute change from baseline in MR relaxivities R1, R2, R2\* at each timepoint post Ferinject infusion, according to the following formulae:

$$\Delta R1 = R1 \text{ (at timepoint x)} - R1 \text{ (at baseline)}$$

$$\Delta R2 = R2 \text{ (at timepoint x)} - R2 \text{ (at baseline)}$$

$$\Delta R2^* = R2^* \text{ (at timepoint x)} - R2^* \text{ (at baseline)}$$

R1, R2, R2\* values are calculated as inverse of T1, T2, T2\* relaxation times obtained by the MR relaxometry or mapping techniques. The results will be reported as time series of average values and standard deviations (median and IQR for nonparametric variables) at each timepoint post Ferinject infusion. The presence of statistically significant signal will be assessed using ANOVA.

The secondary outcome measure is the change from baseline in serum concentrations of iron indices (iron, transferrin saturation, ferritin and non-transferrin bound iron) and markers of tissue iron toxicity (MDA and 4-HNE). Results will be expressed both as absolute change from baseline and as percentage change relative to baseline.

Further exploratory analyses will be performed for possible interactions between the observed measures using correlations, crosscorrelations and pharmacodynamic modelling.

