### **11.2. Sample Size Determination**

The sample size of 12 participants was not arrived at statistically, due to lack of information on the magnitude of effects of Ferinject on R1/R2/R2\* values at early timepoints. However, an exploratory study of MRI imaging following intravenous infusion with ultrasmall superparamagnetic particles of iron oxide (USPIO) at later timepoints used sample sizes of 5-12 participants per group. Of note, the longitudinal design involving repeated measures will increase the statistical power of the study.

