### **11.6. The Level of Statistical Significance**

Tests will be two-sided and considered to provide evidence for a significant difference if p-values are less than 0.05.

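### The 3-hour organ change includes any drug still in the organ's blood, so an early rise does not by itself show tissue uptake

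*Protocol*

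**What the plan says.** Section 5 (Study rationale) states what an early rise would mean. The study asks whether standard treatment produces an acute rise in tissue iron, "including myocardial iron at the early timepoints, which would be evidence for the direct, rapid unregulated route of iron uptake". The same section describes that route as uptake of non-transferrin bound iron (NTBI) through calcium channels. It contrasts this with the usual assumption that macrophages take up the drug and release iron slowly.

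Section 11.1 defines the measure: "The primary outcome is the absolute change from baseline in MR relaxivities R1, R2, R2\* at each timepoint post Ferinject infusion". Each of the three formulae is the value at the timepoint minus the value at baseline. On testing it says: "The presence of statistically significant signal will be assessed using ANOVA". Section 11.6 sets a two-sided 0.05 level.

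Section 9.8 has the 3-hour scan cover "relaxometry of the heart, liver, spleen, blood and skeletal muscle", so blood is measured in the same session as the organs. In section 6 blood appears only as one more compartment in the uptake objective. No section uses the blood value to adjust or qualify an organ value. Section 11 states that no separate SAP is in use, and section 11.8 says the protocol's analysis outline will be followed.

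**The concern.** The drug is infused into blood, and every perfused organ contains blood. An organ's raw relaxation rate at 3 hours therefore mixes the tissue with the blood inside it. Any drug still circulating raises the organ value even when none has left the vessels. The bias would be upward in every participant, so averaging over 12 people would not remove it.

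The 3-hour scan is also the one that carries the mechanistic reading. By 2 and 6 weeks, the slow macrophage route described in section 5 could also have delivered iron, so only the early scan speaks to a rapid route. That scan is the most exposed to circulating drug. The lay summary says the results will be used to design a larger study of potential toxic effects, so a misread early signal could carry forward.

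**Working it through.** There is no figure in the plan to reproduce. Section 11.2 says "The sample size of 12 participants was not arrived at statistically" and gives no effect size, SD or power.

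**Inputs from the protocol:** 1000 mg single infusion (section 6); 12 participants (section 11.2); two-sided 0.05 (section 11.6); uncorrected difference from baseline (section 11.1).

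**Assumptions, none given in the documents:** blood volume 5 L; share of the dose still in blood at 3 hours, 5% or 50-90%; myocardial blood fraction f of 5-15%; simple mixing of blood and tissue.

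**Model:** organ change = f × blood change + (1 − f) × tissue change. With zero uptake the tissue change is 0, and the organ change equals f × blood change.

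**Step 1: apparent iron at zero uptake.** Blood iron from the drug = 1000 mg × share remaining / 5 L. Apparent myocardial iron = f × that value.

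| Share remaining | Blood iron from drug | Apparent, f = 5% | Apparent, f = 15% |
|---|---|---|---|
| 5% | 10 mg/L | 0.5 mg/L | 1.5 mg/L |
| 50% | 100 mg/L | 5 mg/L | 15 mg/L |
| 90% | 180 mg/L | 9 mg/L | 27 mg/L |

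These are concentrations. Turning them into a change in R1, R2 or R2* needs a relaxivity, and judging that change needs a within-person SD. The documents give neither.

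**Step 2: chance of a significant rise at zero uptake.** Without an SD, the blood change can only be written as k SDs of the organ's paired change. The standardised shift is then d = f × k. A two-sided paired t-test with n = 12 stands in for the 3-hour contrast in the ANOVA, with noncentrality d × √12. For example, f = 0.10 and k = 5 give d = 0.50 and noncentrality 1.73, hence 35%. In the upper tail, where chance alone gives 2.5%:

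| k (assumed) | f = 5% | f = 10% | f = 15% |
|---|---|---|---|
| 2 | 5% | 9% | 16% |
| 5 | 12% | 35% | 66% |
| 10 | 35% | 88% | >99% |

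Eighty per cent power at n = 12 needs d = 0.89. Blood alone produces that shift when k is 17.8, 8.9 or 5.9 for f of 5%, 10% or 15%. The table shows how the risk depends on k and f. It does not say where this study lies.

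**Step 3: effect of a blood adjustment.** Adjusted change = organ change − f × same-scan blood change. In 20,000 simulated studies per scenario (blood change varying 20% between people, blood measurement error 1 SD), the two-sided rejection rate at zero uptake was 4.8-5.2% when f was known. With f wrong by 50% at a true f of 10%, it was about 12% for k = 5 and 34-35% for k = 10. Too low an f leaves a false rise; too high an f produces a false fall.

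**The case against.** The strongest reply is that nothing in the protocol says much drug remains in blood at 3 hours. This stands. A reader might infer it from the slow release described in section 5, but the slow step there is release of iron after macrophage uptake, not removal of drug from plasma. A range that starts at 50% remaining would hide the case where the problem is negligible, so the 5% case belongs beside it.

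A reader might also take the cited imaging precedent as proof that circulating iron particles alone change organ signal. Section 11.2 cites "MRI imaging following intravenous infusion with ultrasmall superparamagnetic particles of iron oxide (USPIO) at later timepoints" only to support the sample size, and the documents do not report what that study found about signal source.

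There are partial safeguards. Section 11.1 plans exploratory correlations, cross-correlations and pharmacodynamic modelling, and blood relaxometry is among the observed measures. Serum iron and NTBI are sampled at each timepoint. If the drug has cleared by 2 and 6 weeks, blood would not explain a rise that persists. An artefact that scales with blood content might also be recognisable, for instance as larger in liver and spleen than in heart if those organs hold more blood. These points reduce the risk, but none is a stated rule for reading the 3-hour result.

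Finally, this is a pump-priming study of 12 whose primary objective is kinetics in several compartments, and section 5 speaks of evidence, not proof. That bears on severity. It does not make the uncorrected measure specific to tissue.

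**Conclusion.** The point holds in a limited form. Section 5 reads an early rise as support for direct, unregulated uptake, while the measure in section 11.1 cannot separate tissue iron from drug in the organ's blood. A 3-hour rise caused by circulating drug could therefore be read as uptake.

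The size is unknown. It runs from 0.5-1.5 mg/L apparent myocardial iron (5% of the dose remaining) to 5-27 mg/L (50-90% remaining), under an assumed 5 L blood volume, 5-15% blood fraction and simple mixing. Whether either end would show in R1, R2 or R2* cannot be judged from the documents.

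A reader might go further and conclude that circulating drug alone would be reported as uptake. The documents do not support that, because residual level, relaxivity, blood fraction and SD are all missing. The concern is specific to the 3-hour scan, provided the drug has cleared by the later visits. It should be fixed, but it does not invalidate the study.

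**What to change.** **Section 11.1.** For the 3-hour timepoint, prespecify a sensitivity analysis that reports, for each organ, the change minus (blood fraction × blood change from the same scan). State a range of blood fraction per organ and its source. Show the result across that range, alongside the uncorrected primary result and the blood change itself.

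**Section 5.** Reword the inference so that an uncorrected 3-hour rise shows iron in the organ including its blood, and does not by itself identify the NTBI route. For liver and spleen, add that macrophage uptake is a further explanation even after adjustment.

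A rule that uptake may be claimed only if the adjusted change is positive at the top of the assumed range is not recommended. With f 50% too high the adjustment overshoots (step 3), so such a rule could discard true uptake.

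**Cost.** Protocol wording and a short calculation on data already planned, with no extra scan, sample or participant. The adjusted estimate is noisier and depends on an assumed blood fraction and simple mixing, so it belongs beside the primary result and should not replace it.
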